## **6.2 Exclusion criteria**

Participant exclusion criteria: Currently receiving any other homelessness and/or substance use interventions (outside of The Salvation Army usual care) or participating in the active intervention phase of intervention studies; inability to give clear informed consent due to serious mental illness or cognitive impairment; actively suicidal; posing a safety risk to staff members/Peer Navigators; non-English speaking (due to the intervention involving Peer Navigator relationship and they will not necessarily have languages other than English).

Participation requires ability to provide consent which might be compromised for those with very serious mental illness or cognitive impairment. For people who experience homelessness, severe mental illness is not common (6% bipolar disorder, 6% schizophrenia; [38]) however, prevalence of cognitive impairments can be higher than the general population [39], therefore, clinical expertise from collaborator [name] will support the creation of a recruitment consent protocol.

## **7. Recruitment and randomisation**

### **7.1 Recruitment process**

#### **Recruitment of intervention participants**

The research team will work with the Peer Navigators and The Salvation Army Service Managers (and their delegates, which may include Programme/Project Managers and/or Specialist Support Workers/experienced Support Workers) to identify potential participants. Service Managers, Peer Navigators and their delegates will create a list of people in the service who meet the inclusion criteria. In advance of the researchers coming to the service, an eligibility meeting (via MS Teams) will be held between Service/Programme/Project Managers/Peer Navigators and the Cluster Leads/Chief Investigator/recruiting Researcher. These meetings are designed to build productive relationships and will go through the eligibility criteria in detail, identify how many potential eligible participants there are likely to be, discuss the process of sharing the Participant Information Sheets (PIS) with participants in advance of researchers arriving in service, address any questions the service staff have, and set up the arrangements for the visits. Following the eligibility meeting, if individuals meet the study inclusion criteria a staff member in the service will tell them about the study and provide them with a copy of the PIS prior to the researchers being in the service. If it is not possible to hold an eligibility meeting prior to researchers visiting a service then researchers will work with service staff in person to identify eligible potential participants. When the researchers are in the service, if an individual is interested, a researcher will discuss the study with them, going through the PIS and answering any questions they may have. If they wish to participate, they will be asked to sign a consent form and then their substance use will be checked using the ASSIST-Lite screening tool. Once they have signed a consent form, and they meet the threshold of the ASSIST-Lite screening tool, they will be recruited into the trial and baseline data collection will be arranged. Researchers will visit The Salvation Army services and aim to recruit 25 participants per cluster, under the guidance of the research team. There may be times when there are additional potential participants who were not discussed at the initial eligibility meeting, but who have been identified during the time in which the researchers are in the service. At this point, the recruiting researcher will discuss the potential participant with the Service Manager or their delegate and check they meet

the criteria and then confirm this with the Cluster/Study Leads. Once the participant has been recruited into the study and completed the baseline data collection they will be added to the Peer Navigator's caseload.

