### *Recruitment of standard care participants*

The research team will work with The Salvation Army Service Managers (and their delegates, which may include Programme/Project Managers and/or Specialist Support Workers/experienced Support Workers) to identify potential participants. Service Managers and their delegates will create a list of people in the service who meet the inclusion criteria. In advance of the researchers coming to the service, an eligibility meeting (via MS Teams) will be held between Service/Programme/Project Managers and the Cluster Leads/Chief Investigator/recruiting researcher. These meetings are designed to build productive relationships and will go through the eligibility criteria in detail, identify how many potential eligible participants there are likely to be, discuss the process of sharing the PIS with participants in advance of researchers arriving in service, address any questions the service staff have, and set up the arrangements for the visits. Following the eligibility meeting, if individuals meet the study inclusion criteria a staff member in the service will tell them about the study and provide them with a copy of the PIS prior to the researchers being in the service. If it is not possible to hold an eligibility meeting prior to researchers visiting a service then researchers will work with service staff in person to identify eligible potential participants. When the researchers are in the service, if an individual is interested, a researcher will discuss the study with them, going through the PIS and answering any questions they may have. If they wish to participate, they will be asked to sign a consent form and then their substance use will be checked using the ASSIST-Lite screening tool. Once they have signed a consent form, and they meet the threshold of the ASSIST-Lite screening tool, they will be recruited into the trial and baseline data collection will be arranged. Researchers will visit The Salvation Army services and aim to recruit at least 30 participants per cluster (up to 35 in some clusters to offset control clusters with fewer than 30 participants), under the guidance of the research team. There may be times when there are additional potential participants who were not discussed at the initial eligibility meeting but who have been identified during the time in which the researchers are in the service. At this point, the recruiting researcher will discuss the potential participant with the Service Manager or their delegate and check they meet the criteria and then confirm this with the Cluster/Study Leads.

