
### *Recruitment of Peer Navigators*

The Peer Navigators will be employed by The Salvation Army as part of the study and the research team will already have their contact details because of this. They will be contacted to arrange data collection via interviews, diaries, and outcome measure data collection. There will be one Peer Navigator recruited for each cluster in the intervention arm.

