## **7.3 Informed consent**

We will ensure that participants are recruited in a fair and ethical manner, in line with equality, diversity, and inclusion practices and good research practice. Participants will be asked to provide written informed consent prior to eligibility screening using the ASSIST-Lite tool and baseline data collection, and consent will be checked and recorded at each subsequent data collection timepoint. Participants who are not able to read or write (but who have capacity) can agree to take part in the study. In such cases, the study team will provide them with written literature about the study and read and discuss this information with the potential participant. There will also be a discussion about the support networks that the patient has available to facilitate their participation in the study. If the potential participant is fully informed and wishes to take part in the study, they will be asked to sign or make their mark on the consent form. Their agreement to take part in the study should be witnessed by the Service Manager who will be independent from the research team. While most participants in the SHARPS feasibility study did not report any literacy difficulties, we will ensure that all materials are explained verbally to all participants to ensure they are fully aware of what the study/interviews entail.

All participant materials will be checked by trial Experts by Experience (EbyE) group to ensure they are easy to understand. These materials have been based on those used in the SHARPS feasibility study which were thoroughly reviewed by our EbyE group and learning from that study. All final copies of study materials will be provided to the University of Stirling's NHS, Invasive or Clinical Research (NICR) ethics committee and logged in the trial files. Intervention and control group participants will receive a PIS detailing the study and what is required from them, a consent form, and debrief sheet which will provide participants with information about the study once the study is complete. Both groups will be asked to consent to data collection within the study. In addition, intervention participants will consent to the intervention itself specifically within the general consent form with information on the intervention clearly spelled out in the PIS.

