We aim for the researchers employed solely to collect outcome data at all four time points to be blind to allocation. Full details of the data collection process can be found in section 11 of the protocol. In an attempt to blind Researchers collecting outcome data, all participants will be recruited and consented into the study by members of the research team who are not involved in the quantitative data collection. We will also provide guidance to The Salvation Army staff to ensure they are aware that they must not discuss the study with Researchers. Researchers will be required to record and report any occurrences where the condition of the cluster is revealed to them. We will review any occurrences following each data collection point. However, even if we are unable to maintain blinding of Researchers, data collection will go ahead as planned.

Intervention and control/usual care participants, Peer Navigators, The Salvation Army staff, and core research staff including statisticians and health economists will not be blinded to intervention allocation. Given the nature of the intervention, it is not possible to blind participants and The Salvation Army staff as the presence of Peer Navigators in these services will be known to these groups. It is also useful for statisticians to know which participants are intervention vs. control as this can help with safety in terms of monitoring mental health and other outcomes given the vulnerability of the population. To address potential bias concerns, full plans for statistical analysis of outcome data will be pre-registered (the practice of registering hypotheses, methods, and planned analyses online prior to any data analyses).

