### **21.2 Archiving**

All study documentation will be kept for at least 10 years from the end of the study. Researchers obtaining consent will return consent forms and completed eligibility screening forms (ASSIST-Lite screening tool) to the SHARPS trial office in Stirling where they will be securely stored. If a potential participant did not meet the inclusion criteria (they score below the threshold on the ASSIST-Lite screening tool), all documentation will be shredded on The Salvation Army service premises and not returned to the trial office in Stirling. If electronic data collection is not possible, at the end of each participant's follow-up, Research Assistants will collect the data using paper copies of the questionnaires. Research Assistants are required to input any data they collect using paper copies into the CHaRT data collection tool as soon as the technical issue is resolved. Research Assistants will store any paper copies of anonymised participant data until they have finished collecting the participant data at that timepoint. A courier or tracked delivery will then be arranged to return any paper copies to the University of Stirling for safe storage. Adverse event forms and change of status forms will be completed and returned via email to the study leads at the University of Stirling ([name] and [name] for adverse events and [name] for change of status), or be entered electronically directly onto the SHARPS website database (where the University of Stirling team will be automatically notified by email). Research Assistants and Peer Navigators completing adverse event forms or change of status forms will also inform the study lead ([name]) or Deputy Study Lead ([name]) by phone call that a form has been completed and returned, if there is no response by email after 12 hours. If not captured electronically, once received, all adverse event forms and change of status forms will be recorded in the CHaRT tool by research staff at the University of Stirling. Where appropriate, the study leads at the University of Stirling will follow up with those reporting the incident to ensure that further action has been taken to ensure the safety of those involved. There will be no files stored at the trial sites, all files will either be stored on the SharePoint system, or securely within the University of Stirling or the University of Aberdeen.

Data will be archived by CHaRT for at least 10 years after the end of the study.

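### In intervention clusters only, Peer Navigators help list candidates after allocation is known, an arm-dependent selection risk that baseline data can check only in part

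*Protocol*

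**What the plan says.** Section 7.1 of the protocol describes recruitment separately for each arm.

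- Intervention clusters: "Service Managers, Peer Navigators and their delegates will create a list of people in the service who meet the inclusion criteria". Peer Navigators also attend the eligibility meeting with the cluster leads or the recruiting researcher. Participants join the Peer Navigator's caseload after baseline data collection.
- Control clusters: "Service Managers and their delegates will create a list of people in the service who meet the inclusion criteria". The meeting is held without any counterpart to the Peer Navigator.

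Section 7.1 also states "There will be one Peer Navigator recruited for each cluster in the intervention arm". Under section 7.3, "intervention participants will consent to the intervention itself specifically within the general consent form". Section 7.4 says: "Intervention and control/usual care participants, Peer Navigators, The Salvation Army staff, and core research staff including statisticians and health economists will not be blinded". The same section separates recruitment from measurement: "all participants will be recruited and consented into the study by members of the research team who are not involved in the quantitative data collection".

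In both arms a researcher applies the ASSIST-Lite threshold after consent. For people who fall below it, section 21.2 says that "all documentation will be shredded on The Salvation Army service premises and not returned to the trial office in Stirling". Section 14.3 describes baseline data by group and adjusts the primary model for country and the baseline outcome score.

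**The concern.** When participants are identified after their cluster's arm is known, randomisation of clusters no longer guarantees comparable participants. The safeguard is then that candidates are found in the same way in both arms. Here they are not. In one arm the person who will work with the participants for 12 months helps decide whose names go forward, and in the other arm that role does not exist. Without any intent, such a person may favour people who seem likely to engage, or people in greatest need.

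Both co-primary outcomes are self-reported and participants are unblinded, so the comparison depends heavily on the two groups being alike at entry. A difference in motivation or stability that the baseline PHQ-ADS or ICECAP-A score does not capture would pass into the treatment effect.

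**Working it through.** **1. Is allocation known at listing?** No single sentence gives the order, but it follows from the text. Peer Navigators exist only in intervention clusters and take part in listing. The per-cluster target differs by arm (25 against at least 30, up to 35 in some clusters). Consent content differs by arm. The Peer Navigators and service staff are unblinded.

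**2. Which safeguards act on listing?**

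| Safeguard | Where it acts |
|---|---|
| Recruiters separate from data collectors (7.4) | Outcome measurement |
| ASSIST-Lite threshold, same in both arms (7.1) | After listing and consent; cannot restore people never listed |
| Pre-registered analysis (7.4) | Analysis choices |
| Adjustment for country and baseline score (14.3) | Only the part of selection carried by those variables |

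None makes the listing step the same in the two arms.

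**3. The plan's own figure (section 14.1).** Inputs: 10 x 25 = 250 and 10 x 30 = 300 recruited; 250 x 0.60 = 150 and 300 x 0.50 = 150 analysed; mean cluster size 15; ICC 0.01; effect 0.4 SD. Two-sided 5% is assumed, in line with the 95% intervals.

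- Design effect: 1 + (15 - 1) x 0.01 = 1.14
- Effective n per arm: 150 / 1.14 = 131.6
- Power for 0.4 SD: 90.05% (normal approximation), which matches the stated 90%
- SE of the effect: sqrt(2 x 1.14 / 150) = 0.123 SD

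The power figure is sound and does not bear on selection. It supplies the SE for the next step.

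**4. Illustration of what a residual difference would do.** The documents give no size for a selection effect, so the range is assumed. With b the difference in SD left after adjustment and no true effect, the two-sided rejection rate is P(|Z + b/0.123| > 1.96), or its t equivalent on 18 df (20 clusters minus 2, also assumed). The implied PHQ-ADS SD is 5 / 0.4 = 12.5 points.

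| b (SD) | PHQ-ADS points | Error rate, normal | Error rate, t 18 df |
|---|---|---|---|
| 0.05 | 0.6 | 7% | 7% |
| 0.10 | 1.25 | 13% | 12% |
| 0.15 | 1.9 | 23% | 21% |
| 0.20 | 2.5 | 37% | 34% |

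The SE takes no credit for baseline adjustment or repeated measures. With a smaller SE, the same b would raise the error rate further.

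**5. How well could a baseline comparison reveal it?** Design effects at baseline are 1 + 24 x 0.01 = 1.24 and 1 + 29 x 0.01 = 1.29. SE = sqrt(1.24/250 + 1.29/300) = 0.096 SD. Power to detect an imbalance is about 18% at 0.10 SD and 55% at 0.20 SD; 80% power needs about 0.27 SD. A balanced baseline table would therefore be weak reassurance about differences of 0.10 to 0.20 SD.

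**The case against.** The case for the plan has real substance, and four stronger readings should not be drawn from the text.

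- **That bias is built in.** A reader might infer this, but the documents support only a risk. The list is meant to hold everyone who meets the criteria, and no ranking is described. Service Managers and delegates co-create it in both arms. Late candidates are checked by the Service Manager or a delegate and confirmed by the cluster or study leads, with no Peer Navigator role stated. Peer Navigators are recruited for the trial, so how well they know the service's clients at that point is unknown. The direction of any effect is open.
- **That it cannot be checked.** It can, in part. Table 1 has CEST treatment engagement, treatment need and psychological functioning, LDQ, MAP, SSQ and housing status at baseline in both arms. Section 11.1 adds demographics, care history and medication. Baseline data come before the caseload begins, from researchers intended to be blind. These are useful proxies for engagement and stability, though they cannot exclude unmeasured differences, and small imbalances are hard to see.
- **That shredding destroys the evidence of selection.** It does not. The rule covers people already listed and consented who then fall below the ASSIST-Lite threshold, in both arms. Someone never listed leaves no form to shred, and the rule does not forbid an anonymous count. The more relevant gap is that the protocol describes no log of people listed, approached or declining. A working procedure not shown may provide one.
- **That a safety exclusion is judged differently by arm.** The criterion reads "posing a safety risk to staff members/Peer Navigators", so it covers staff in both arms, and section 6.2 does not say who judges it.

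What stands is the difference in who lists and who attends the meeting, after allocation is known.

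**Conclusion.** The point holds as an arm-dependent risk of selection bias, of unknown size and direction. It rests on the text of sections 7.1, 7.3 and 7.4 and needs no numerical assumption. The existing safeguards protect other steps, and comparison of baseline measures by arm gives only a partial check. The error rates of 7% to 37% for residual differences of 0.05 to 0.20 SD are illustration only: they show how sensitive the result would be, not how biased it is. The change is worth making because it is cheap and because control clusters already list in the proposed way.

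**What to change.** Amend section 7.1 so that Service Managers and their delegates compile the candidate list by the same written procedure in both arms, with no Peer Navigator in listing or in the eligibility meeting.

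As a secondary step, amend section 21.2 so that an identifier-free tally per cluster reaches the trial office before any form is destroyed: listed, approached, declined, consented, ASSIST-Lite pass or fail, and reason excluded. Report it by arm. This keeps the privacy purpose of the shredding rule.

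Recruitment may already be over. Section 14.7 places it in months 7 to 10 of a trial starting in April 2024, which is October 2024 to January 2025 if April is month 1, and the version 4 changes largely concern follow-up. If it has closed, reconstruct these counts from retained records where possible, compare baseline CEST scales, LDQ, MAP, housing status and demographics by arm, and state the limitation in the report.

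The cost is a short amendment and a one-page tally form. The downside is that Peer Navigators' input at listing is lost.

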### *Recruitment of standard care participants*

The research team will work with The Salvation Army Service Managers (and their delegates, which may include Programme/Project Managers and/or Specialist Support Workers/experienced Support Workers) to identify potential participants. Service Managers and their delegates will create a list of people in the service who meet the inclusion criteria. In advance of the researchers coming to the service, an eligibility meeting (via MS Teams) will be held between Service/Programme/Project Managers and the Cluster Leads/Chief Investigator/recruiting researcher. These meetings are designed to build productive relationships and will go through the eligibility criteria in detail, identify how many potential eligible participants there are likely to be, discuss the process of sharing the PIS with participants in advance of researchers arriving in service, address any questions the service staff have, and set up the arrangements for the visits. Following the eligibility meeting, if individuals meet the study inclusion criteria a staff member in the service will tell them about the study and provide them with a copy of the PIS prior to the researchers being in the service. If it is not possible to hold an eligibility meeting prior to researchers visiting a service then researchers will work with service staff in person to identify eligible potential participants. When the researchers are in the service, if an individual is interested, a researcher will discuss the study with them, going through the PIS and answering any questions they may have. If they wish to participate, they will be asked to sign a consent form and then their substance use will be checked using the ASSIST-Lite screening tool. Once they have signed a consent form, and they meet the threshold of the ASSIST-Lite screening tool, they will be recruited into the trial and baseline data collection will be arranged. Researchers will visit The Salvation Army services and aim to recruit at least 30 participants per cluster (up to 35 in some clusters to offset control clusters with fewer than 30 participants), under the guidance of the research team. There may be times when there are additional potential participants who were not discussed at the initial eligibility meeting but who have been identified during the time in which the researchers are in the service. At this point, the recruiting researcher will discuss the potential participant with the Service Manager or their delegate and check they meet the criteria and then confirm this with the Cluster/Study Leads.
